### Additional Consent Provisions for Collection and Use of Participant Data and Biological Specimens

A part of informed consent will be dedicated to reusing the data obtained in the proposed study to improve the proposed statistical model or the development of a novel predictive statistical model. The study conforms to the Consolidated Standards of Reporting Trials (CONSORT) guidelines.

### Interventions

#### Explanation for the Choice of Comparators

Not applicable. The comparator is not used in this study.

#### Intervention Description

Assessment 0 includes screening for eligibility criteria and obtaining baseline data on subjects participating in the study. After signing the informed consent, the patient will be given a unique code with which all data will be labeled. The demographic information, health history, including psychiatric disease and type of epilepsy, concomitant medication (ASM and other drugs), and seizure frequency will be collected. The seizure frequency will be analyzed based on the patient diary. Standard EEG will be recorded according to the protocol described below. Patients will be asked to fill in a questionnaire focusing on the quality of life.

### Protocol for EEG Recording

The EEG will be recorded on the EEG recording system with a sampling frequency of 250 Hz or higher, with electrodes placed on the scalp according to the 10–20 system (with the following electrodes: Fp1, Fp2, F7, F3, Fz, F4, F8, T3, C3, Cz, C4, T4, T5, P3, Pz, P4, T6, O1, and O2). Different electrode names are allowed, but their position must correspond with the position of the previously defined electrodes. Additional electrodes are also allowed, but will not be evaluated within the study. EEGs with fewer or differently-positioned electrodes are not allowed.

The EEG is recorded in a supine position with eyes closed, except for periods with opening of eyes. The recorded EEG will have a duration of 20 min or more and must contain defined segments in the following order as in Table 1.

**Table 1 T1:** Predefined segments ordering in the course of EEG recording.

Segment 1	Rest 1	duration at least 2 min
Segment 2	Eyes opening/closing	duration at least 10 s
Segment 3	Rest 2	duration at least 10 s; immediately after eye closure
Segment 4	Photic stimulation	stimulation frequencies: 5 Hz (10 s)−10 Hz (10 s)−15 Hz (10 s)−20 Hz (10 s)−25 Hz (10 s)−30 Hz (10 s)−25 Hz (5 s)−20 Hz (5 s)−15 Hz (5 s)−10 Hz (5 s)−5 Hz (5 s); light intensity at least 0.7 Joule
Segment 5	Hyperventilation	duration at least 4 min (2 min hyperventilation by nose + 2 min hyperventilation by mouth)
Segment 6	Eyes opening/closing	duration at least 10 s
Segment 7	Rest 3	duration at least 10 s, immediately after eye closure
Segment 8	Rest 4	duration at least 2 min

The recorded EEG will be anonymized and labeled by a unique code previously attributed to a patient. In the next step, the EEG will be sent for mathematical/statistical processing. Based on this processing, the patients' predicted response to VNS will be determined in terms of predicted responders (seizure reduction ≥50%) vs. predicted non-responders (seizure reduction <50%). Neither the patient nor the physician will be informed about the classification results.

Two assessments are designed for patients' follow-up:

Assessment 1−1 year after stimulation initialization, and

Assessment 2−2 years after stimulation initialization.

The patients will be evaluated 1 and 2 years after the start of VNS therapy. The patient will be requested to report any changes in health history, including psychiatric disease, and specific requests will be focused on changes in medication (ASM and other drugs), VNS parameters settings, and seizures. The patients will be asked whether unexpected events influenced their clinical response. If these unexpected events are regarded as “clinically highly important” (such as non-compliance or other newly-diagnosed disease worsening epilepsy), the patient can be excluded based on clinical decision. The data on seizure frequency will be collected by reviewing the patient's diary. The reported seizure frequency will be compared with pre-implantation seizure frequency, and real-life response will be calculated in terms of real-life responders (seizure reduction ≥50%) or real-life non-responder (seizure reduction <50%). The patients will fill in a questionnaire focusing on the quality of life. If the patient does not tolerate at least the minimal VNS settings (0.75 mA) because of serious adverse events, they will be excluded from further analysis (the patient's data will be reported separately). The patients included in our study will be managed according to the best clinical praxis, i.e., the change of ASM and VNS parameters will be done based on the clinicians' decision to reflect the real-life response.

The information collected in Assessments 1 and 2, including real-life response to VNS, will be labeled with the patient's unique code and sent to the coordinating center, where it will be compared with the patient's predicted response.

At the end of Assessment 2, patients will be asked if they are interested in the predicted response to VNS. If the answer is yes, the study physician will contact the coordinating center, where the predicted response for a given patient will be conveyed. The patient will be informed about the predicted response by telephone or during a regular visit (not a part of the study protocol, described below).

### Criteria for Discontinuing or Modifying Allocated Interventions

If a patient does not tolerate at least the minimal VNS setting (0.75 mA) because of serious adverse events, the patient will be excluded from further analysis (the patient's data will be reported separately).

### Strategies to Improve Adherence to Interventions

Training before initialization will ensure the fidelity during the whole study. If there are doubts, the coordinating center will solve them.

### Relevant Concomitant Care Permitted or Prohibited During the Trial

Regular visits—not part of the study protocol.

There are regular visits between Assessments 0, 1, and 2. The regular visits are not part of the study protocol. The physician will adjust the VNS parameters and change concomitant ASM according to the best clinical practice to obtain the best response with minimal side-effects. The regular visits will be scheduled according to the individual habits of cooperating centers. The change of ASM (types and dosing) is allowed within the whole study.

### Outcomes

The primary outcome of the study is the accuracy of the statistical model for prediction of response to VNS therapy in drug-resistant epilepsy, expressed as a percentage of correct predictions (responders vs. non-responders), evaluated after 2 years.

The secondary outcomes of the study are the quantification of differences in EEG power spectra (Relative Mean Power, %) between real-life responders and real-life non-responders to VNS therapy in drug-resistant epilepsy and the prediction of patients' response to VNS therapy in terms of responders, expressed as sensitivity of the model, and non-responders expressed as specificity of the model. If possible, these data can be used for further improvement of the statistic model.

The study is concerned with the verification of the real-life validity of our statistical classifier for the prediction of VNS response based on pre-implantation EEG data. The patients will be classified based on their predicted response as predicted responders (≥50% seizure reduction) and predicted non-responders (<50% seizure reduction). In Assessments 1 and 2, respectively, the patients' real-life response will be determined: real-life responders (≥50% seizure reduction) vs. real-life non-responder (<50% seizure-reduction). The predicted and real-life responses will be statistically compared in terms of accuracy, sensitivity, and specificity.

The individual patients' groups (predicted responders vs. predicted non-responders, real-life responders vs. real-life non-responders) will be compared based on their demographic data, health history, ASM, and VNS parameters. A suitable statistical test will be chosen concerning the characteristics of the data (Pearson's Chi-squared test for categorical variables, and Wilcoxon-Mann-Whitney test for continuous variables).

### Participant Timeline

The schedule of enrolment, intervention and visits is summarized in Table 2. The study is focused on patients indicated to VNS therapy as their standard for clinical care and is concerned with the prediction of VNS efficacy based on pre-implantation EEG. The duration of the study participation in a given patient is 2 years.

**Table 2 T2:** Participant timeline.

	**Assessment 0**	**Assessment 1**	**Assessment 2**
	**Day 0**	**Year 1**	**Year 2**
Screening—inclusion/exclusion criteria	X		
ICF	X		
Demographic information	X	X	X
Health history	X	X	X
Concomitant medication	X	X	X
Seizure frequency	X	X	X
EEG	X		

*Between assessment 0 and Assessment 1, VNS will be performed, but it is not a part of this study*.

### Sample Size

The sample size was estimated for the primary endpoint, which was defined as the accuracy of the statistical model for prediction of response to VNS therapy in terms of responders and non-responders in drug-resistant epilepsy. During the verification of the validity on the independent dataset, the model was able to predict the response to VNS with 86% accuracy. The minimal clinically significant accuracy was set to 70%. The sample size is estimated for the following hypothesis:

Hypothesis H0: *p* = 0.7 vs. Hypothesis H1: *p-value* > 0.7.

At the level of significance α = 0.05 and with a power of 90%, the number of patients needed for the analysis of the primary endpoint is 57. Assuming a drop-out rate of 50%, a total number of 114 patients should be enrolled.

### Recruitment

Recruitment of the patients is planned from January 2022. During the first 2 years, the total planned number of 140 patients will be recruited. The patients will be recruited within cooperating epilepsy centers. The recruitment limited to cooperating centers will ensure the correct indication for VNS therapy and the adjustment of VNS parameters according to the best medical practice, which are not part of the study protocol itself, but are crucial for the study results.

The VNS will be indicated in a particular patient based on a clinical decision as a standard of the patient's therapy (i.e., the indication of VNS is not a part of the proposed project). The patient will be informed about the study on a pre-implantation visit or by a telephone call, during which initial eligibility for the study will be determined, and the study protocol and design will be explained by the research staff.

### Assignment of Interventions: Allocation

#### Sequence Generation

Not applicable. This study is not randomized.

#### Concealment Mechanism

Not applicable. This study is not randomized.

#### Implementation

The study investigator enrolls the participants. The other collaboration centers are responsible for patients' selection according to eligibility criteria, adherence to all criteria of study as described below, and adjustment of ASM and VNS therapy according to the best clinical practice, and enrolling the participants.

### Assignment of Interventions: Blinding

#### Who Will Be Blinded?

Not applicable. This study is not blinded.

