## Methods and Analysis

### Study Setting

The PRECISE study has not yet been recruited. The study is planned to be initiated in nine European countries (Czech Republic, France, Germany, UK, Spain, Austria, Portugal, Italy, and Belgium) in 2022.

Brno Epilepsy Center, the coordinating center for the study, is responsible for education and training of research staff, tracking participants' enrolment, mathematical analysis, including statistics of scalp EEG, and reporting of the study.

The other collaboration centers are responsible for patient selection according to eligibility criteria, adherence to all criteria of the study as described below, and adjustment of ASM and VNS therapy according to the best clinical practice.

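### Masking to the prediction is stated inconsistently, does not reach those who decide exclusions, and ends for each patient without a locked outcome

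*Protocol article*

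**What the plan says.** All references are to the Protocol article.

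- **Blinding.** Under Who Will Be Blinded? the answer is "Not applicable. This study is not blinded". The section on unblinding repeats it.
- **Withholding.** Protocol for EEG Recording states: "Neither the patient nor the physician will be informed about the classification results".
- **Release.** The follow-up text of the same section states: "At the end of Assessment 2, patients will be asked if they are interested in the predicted response to VNS". If the patient wishes to know, "the study physician will contact the coordinating center, where the predicted response for a given patient will be conveyed".
- **Who holds what.** Study Setting makes the coordinating center responsible for "mathematical analysis, including statistics of scalp EEG, and reporting of the study". The follow-up text sends the outcomes of Assessments 1 and 2 to that center for comparison with the predictions.
- **Exclusions.** The follow-up text allows a patient to be excluded by clinical decision after an important unexpected event. The section on non-adherence and missing data defines no analysis populations. It leaves non-adherence to the principal investigator's judgement in each case and removes major deviators from the analysis. Data Management has the statistician analyse the data together with a principal investigator.
- **Custody.** The Oversight section says that no coordinating center will be established, although Study Setting names one.

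**The concern.** The primary endpoint is the percentage of correct predictions. The main safeguard in such a study is that whoever settles the outcome, or decides whether a patient counts, does not know the prediction. The article practises this masking for two parties and denies blinding in the section meant to describe it. It is silent on the people best placed to know both sides.

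The outcome leaves room for judgement. Response is a dichotomy at 50% seizure reduction, based on diaries, and the Discussion itself calls the evaluation of seizure frequency the most debatable part of the protocol. Exclusions also leave room, because they rest on individual judgement and the sample size already allows for losing half of those enrolled. If either decision is made or revised with the prediction in view, disagreements are the cases most likely to be re-examined, and accuracy moves upward.

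**Working it through.** **1. Who is masked, and until when**

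| Role | What the article says about knowing the prediction |
|---|---|
| Patient | Not informed; may ask at the end of own Assessment 2 |
| Physician | Not informed; obtains it from the coordinating center when the patient asks |
| Coordinating center | Produces the predictions and receives the outcomes; no masking stated for any of its staff |
| Those who decide exclusions, including the principal investigator | No masking stated |

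As written, a site physician does not know the prediction while the patient is followed. The gap lies in the last two rows, and in the period after release if the record can still be edited.

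**2. How long a disclosed record could stay open**

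Recruitment states: "During the first 2 years, the total planned number of 140 patients will be recruited". Participant Timeline states: "The duration of the study participation in a given patient is 2 years". If recruitment fills the 24 months and the time from enrolment to start of stimulation is similar across patients, Assessment 2 dates spread over about 24 months. With no lock for the individual patient, the first patient's outcome and exclusion status could stay editable for about that long after disclosure.

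**3. The plan's own sample size**

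Inputs from Sample Size: null accuracy 0.70, expected accuracy 0.86, one-sided alternative, alpha 0.05, power 90%.

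n = [(1.645 × √(0.70 × 0.30) + 1.282 × √(0.86 × 0.14)) / 0.16]² = [(0.754 + 0.445) / 0.16]² ≈ 56.1, rounded up to 57.

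The exact one-sided binomial test also gives 57 as the smallest size with at least 90% power. Success then needs 46 or more correct predictions (alpha 0.0486, power 0.906). With 50% drop-out, 57 / 0.5 = 114. Both stated figures reproduce, and masking does not alter them.

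**4. What unmasked decisions could do**

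The shares below are assumptions; the article gives no rate of borderline diaries or of contested exclusions. True accuracy is set at 0.70, so any success is false. The expected number of wrong predictions among 57 is 57 × 0.30 = 17.1, so 5%, 10% and 20% correspond to about 0.9, 1.7 and 3.4 patients.

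- Reclassification: if a share q of wrong predictions is turned into agreement, apparent accuracy = 0.70 + 0.30q.
- Selective exclusion: if a share e of wrong predictions is dropped, apparent accuracy = 0.70 / (0.70 + 0.30(1 − e)), with 57 analysed.
- Chance of false success = P(X ≥ 46) for a binomial with n = 57 at that accuracy.

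| Assumed share | Accuracy, reclassified | False success | Accuracy, excluded | False success |
|---|---|---|---|---|
| 0% | 0.700 | 0.049 | 0.700 | 0.049 |
| 5% | 0.715 | 0.078 | 0.711 | 0.068 |
| 10% | 0.730 | 0.121 | 0.722 | 0.095 |
| 20% | 0.760 | 0.254 | 0.745 | 0.178 |

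**The case against.** **The blinding entry may be a template answer.** It stands under Assignment of Interventions, next to entries saying that the study is not randomized, and can be read as a statement about open treatment. That is plausible, and it makes the conflict one of wording. It does not show who is masked to the prediction beyond the two parties named.

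**Release cannot steer treatment.** A reader might infer that disclosure makes the prediction self-fulfilling through drug or stimulator adjustment. The article does not support this. Release comes at the end of the patient's own Assessment 2, after that patient's in-study treatment and seizure review, and the physician is not informed before then.

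**Staggered release does not unmask others.** A reader might also infer that disclosing early finishers biases patients still in follow-up. One patient's prediction says nothing direct about another's. The stagger matters only for how long an unlocked, disclosed record remains open.

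**The coordinating center is not said to determine response at other sites.** This is correct; it receives and compares. The concern there is the exclusion decisions and any later query on an outcome.

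**Access rights and record locking are often left to a full protocol or data-management plan.** This is fair, and their absence from an article would not by itself be a finding. Here, however, the article answers the blinding question in conflict with another section, grants discretion over exclusions and fixes the moment of release. If the full protocol already contains the masking and the lock, only the wording needs aligning.

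**Conclusion.** The point holds in limited form. The entries on blinding and on withholding the prediction conflict and must be reconciled. As described, masking stops at the patient and the physician. It does not reach those who decide exclusions or the center that holds both predictions and outcomes. Release is not tied to a locked outcome and exclusion status. Followed as written, this leaves a route by which accuracy can be overstated.

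The size is illustrative. At true accuracy 0.70, acting on 10% of wrong predictions (fewer than two patients expected) would raise false success from 0.049 to 0.121 by reclassification or 0.095 by exclusion. This rests on the assumed shares, on 57 analysed patients and on all changes favouring agreement.

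A reader might note that 43 of 57 correct gives one-sided p = 0.229 and 46 of 57 gives p = 0.0486, and conclude that three altered outcomes would decide the trial. The p-values are right, but three changes in one direction from exactly 43 is a constructed case. It shows how few patients separate failure from success and does not estimate bias. Nothing in the article suggests that outcomes would be altered improperly. The change should be made before any prediction is released.

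**What to change.** Replace the two entries under Blinding with a statement along these lines: *Treatment is open. Patients, treating physicians, those who determine the real-life response and those who decide on exclusions, including the principal investigator and clinical staff of the coordinating center, are masked to the prediction. The EEG analysts hold the predictions in an access-restricted file.*

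In the follow-up text, add: *A patient's prediction is released only after that patient's Assessment 2 outcome and exclusion status have been entered and locked.*

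State in the section on non-adherence that exclusions are decided without knowledge of the prediction. Reconcile the Oversight entry with Study Setting, so that it is clear who keeps the predictions.

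The cost is wording, access rights in the existing RedCap database, a separation between those who analyse the EEG and those who decide exclusions, and a short delay before some patients learn their prediction. Waiting for the lock of the whole database is not needed for this purpose. No recalculation of sample size is required.

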#### Procedure for Unblinding If Needed

Not applicable. This study is not blinded.

### Data Collection and Management

#### Plans for Assessment and Collection of Outcomes

The study will collect demographic and baseline characteristics from medical records and electronic medical records, including age, sex, type of admission, and baseline characteristics such as body weight, body height, patient history, and pharmacological history. Results of EEG tests and neurological assessment will be documented in the electronic medical records and entered by the trial investigator in the electronic case report form (eCRF).

#### Plans to Promote Participant Retention and Complete Follow-Up

The study site will make every reasonable effort to follow the participant for the entire study period. Study site staff members will be responsible for developing and implementing local standard operating procedures to achieve maximal follow-up.

#### Data Management

The study data will be entered online in an Internet-based database (RedCap®) and collected from medical records. The study staff members will have access to the medical records of the patients. Investigators will be responsible for screening the patients, obtaining informed consent, collecting study data, and entering the data in the eCRF. A statistician will analyse the study data in cooperation with a principal investigator. The data will be stored for 15 years after completion of the study and then destroyed. To promote data quality, the eCRFs of each participant will be reviewed by another member of the study team as monitor.

#### Confidentiality

All study-related information will be stored securely at the study site. All participant information will be stored in locked file cabinets in areas with limited access. All local databases will be secured with password-protected access systems. Forms, lists, logbooks, appointment books, and any other listings that link participant ID numbers to additional identifying information will be stored in a separate locked file in an area with limited access.

### Plans for Collection, Laboratory Evaluation, and Storage of Biological Specimens for Genetic or Molecular Analysis in This Trial/Future Use

Not applicable. In this study, no biological specimens for genetic or molecular analysis will be collected.

